Interoception is described as the perceived sense of the physiological condition of the body [1] which is distinguished from exteroception that is characterized by the code of information deriving from somatic motor activity [2]. The first representation of the interoceptive information is on the posterior-dorsal insula conrtex [2] and subsequently integrated into the right anterior insula [2, 3], hence the information is projected towards the amygdala and the nucleus accumbens [ 4] and towards the orbito-frontal cortex [2, 5]. Therefore, the insula is strategically positioned to receive and integrate interoceptive information [6] and exteroceptive and integrate them with emotions and memory giving the perception of the self and how the self is perceived [7, 8]. In addition, data from other studies extended the role of multimodal convergence of the insula. Indeed, it seems to be involved in gustatory responses, homeostatic processes, in vestibular function, attention, pain, emotion, verbal and motor information, as well as on olfactory, visual, auditory and tactile sensations [1-3, 9]. This functional feature of convergence of numerous and different information lays the foundations for a cinemascopic representation model of perceptions of self argued by Craig as "sentient self" [8] that underlies the insula's ability to generate global emotional moments over time, second by second [8, 10]. Moreover, the insula seems to be the central hub of the "salience network" (SN), which includes the dorsolateral prefrontal cortex and the anterior insula, in the complex called fronto-insular cortex [11] and acts as a mediator of information in the cognitive representation of self. This SN is one of the two "functional connectivity" circuits (FC) to which the insula participates. The first, anterior, has as its distinctive elements the ventral anterior insula, the rostral anterior cingulate cortex, the inferior and medial frontal cortex, and the temporoparietal cortex. The second, instead, is characterized by the presence of the posterior dorsal insula, the posterior-dorsal cingulate cortex, the sensorimotor, premotor, supplementary motor, the temporal cortex and some occipital areas. The two circuits serve two different functions: the first to elaborate the interoceptive information and control the patterns of attentional processing, therefore mainly involved in the functions of cognitive integration, homeostatic, emotional, interoceptive awareness and control of the arousal during cognitive tasks. [12-14]; the second control of motor function, environmental and selective response [2, 15, 16].

The correlations between the various brain areas appear to be exclusive. In fact, the individual structures of each network seem to be anti-correlated. This reinforces the idea that the two portions of the insula underlie different functions and are connected to different networks that work independently [17].

One way to measure the functional connections between the various brain areas is during the "resting state" condition, in which the subject is in the absence of stimuli. Fluctuations of brain activity are recorded using fMRI with BOLD technique [18]. This allows to highlight spontaneous activity patterns known as resting state networks (RSN) [13, 17, 19, 20]. The properties of the BOLD signal of the RSN seem to be consistent between individuals and stable between different measurement sessions [21-23]. The SN and therefore the insula circuits have also been studied in the field of RSN, with more precise areas of brain involvement [11, 12]. Menon and Uddin have hypothesized that the right anterior insula acts as a causal center of efference that coordinates two important networks of executive (external, posterior insula) and interoceptive (internal, anterior insula) control [11]. Thus the connection hypotheses formulated by Craig [1-3, 24] as well as the SN [11, 12] define the role of the right insular cortex as a pivotal region in the brain's attentive system [25, 26].

Moreover, some authors have studied the activation of the insula cortex in relation to specific tasks: interoceptive (heartbeat [27] or breath [28]) and exteroceptive [29], showing significantly different behaviors.

Chronic pain is one of the most frequent chronic disorders and has the highest prevalence in people with low back pain (cLBP), which is the main cause of economic and financial loss in terms of cost per treatment and days of work lost [30]. In Europe, the prevalence of cLBP varies from country to country. In Italy the prevalence of cLBP is approximately 6% [31]. While there is a high level of knowledge of the peripheral and spinal neurological mechanisms of chronic pain, evidence about central changes is emerging [32]. Numerous studies on the central mechanisms of chronic pain refer to neurogenic (or neuropathic) pain [33] which appears to be related to thalamocortical patterns measured both by EEG [34, 35] and by fMRI [3, 36, 37]. Furthermore, chronic pain seems to be related to specific cerebral fluctuations [38]. Evidence suggests that different brain structures are responsible of central changes in subjects with chronic pain [39], in particular the anterior circuit of the insula thus the anterior insula and the anterior cortex of the cingulum [40]. However, authors suggested the predominance of the medial prefrontal cortex [41]. Moreover, Apkarian et al (2011) estimated that by analyzing the activity of the medial prefrontal cortex and insula it could be estimated the magnitude and duration of lumbar pain with a margin of error of 20% [41]. Furthermore, Malinen et al showed that subjects with chronic pain have a condition of activation of abnormal RSN, with a higher activity frequency on insula and on the anterior cingulate cortex [42]. Numerous types of interdisciplinary treatments, including manipulative therapies, have been proposed to improve clinical outcomes in patients with cLBP [43]. However, there is still little evidence of the possibility of changes in brain activity in subjects with chronic pain using manual therapies, for example with an osteopathic approach. The osteopathic model uses a system of manual evaluation of the patient, defined osteopathic analysis, in order to highlight the presence of somatic dysfunctions (codes M99.00-09 classes ICD10), that is body districts with mobility restriction. Osteopathy addresses somatic dysfunctions through appropriate manual methods (OMT), with the aim of normalizing them [44]. The manual analysis with osteopathic modality is addressed to the analysis of body movements in order to highlight the mobility limitations of the single joints. The objective of this study is to evaluate the effect of osteopathic treatment on functional connectivity and on insula activity and therefore of the anterior circuit of the SN, both in resting state and during an 'interoceptive awareness' - IA - (heart rate) or 'exteroceptive awareness' - EA - (time count) task in a sample of subjects suffering from cLBP. This could shed light on the central effect of manual treatment with osteopathic modality, laying the first bases for understanding neural mechanisms.

MATERIALS AND METHODS

PURPOSE OF THE STUDY

The main aim of the present randomized controlled two-arm and single-blind study is to evaluate the change in activation and connectivity of the anterior cortex of the insula and the medial prefrontal cortex between before and after the period of manual treatment with osteopathic modality. Secondary goals are:

I) to monitor the differences of activity and FC of the SN between the study group and the sham control;

II) to monitor the intra-group differences and the intergroup of activities and of the CF of the SN immediately after the first treatment;

III) to monitor the differences in activity of intra-group and inter-group RSN during the treatment period;

IV) to monitor the differences in the IA and EA both within and between groups;

V) to evaluate the DTI structural differences;

VI) to evaluate differences in terms of GABA concentration in the anterior insula by means of

MRS

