**MRI DATA PROCESSING**

The functional, structural and spectroscopic magnetic resonance data will be analyzed with dedicated software (AFNI, FSL, JMRUI) or specifically developed at ITAB, obtaining both individual and group functional activation and connectivity maps. Differences in activity and connectivity pre / post or between groups in the insula and other regions of interest will be evaluated through linear mixed effect models.

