**STATISTIC ANALYSIS**

The lack of literature on precise estimate of the effect (effect size) of the manual treatment with osteopathic modality on the main outcome limits the calculation of the sample size. Therefore, given the lack of research measuring these effects at the brain level using fMRI, it is rather difficult to have a precise effect-size estimation. However, in general, the estimates reported in the literature for the expected effect-size with fMRI measures (eg comparison of connectivity values between different populations as in Greicius et al., 2007) indicate relatively high values (Cohen ‘s d= 1.01). This effect-size, together with an alpha and beta value of 0.05 and 0.8 respectively as usual in neuroimaging studies (Desmond et al., 2002) have been included in the R Statistical program to estimate the sample size, resulting in N=16 subjects per group.

Statistical analysis will be based on the 'intention-to-treat' and 'per-protocol' method. The statistical analysis will use the mean and standard deviation, median and percentiles, percentage points for the description of the variables of the two groups. The analyzes will be standardized by age and gender. The hypothesis H0 (null hypothesis) is the non-difference between the two groups at the end of the treatment. To test this hypothesis the assumption of the normal distribution of data through the Shapiro test will be tested first.

The analysis of residuals indicates the possible use of logarithmic transformations of the data. Subsequently the univariate analysis foresees the use of the analysis of the variance (ANOVA) for the comparison of the numerical variables, while the chi square (chi-square test) for the categorical and / or ordinal variables. Primarily used for the comparison of the two samples to the baseline, with the same method we will also analyze the data at the end of the treatment taking into account the inability to detect the independent effect of the variables on the outcome. ANCOVA will be used to explore in greater detail the treatment effect considering cofactors. Multivariate analysis will include the use of the best weighed model for confounding and interaction factors.

The level of statistical significance is established for an alpha <0.05. A post-hoc power calculation will be carried out.

Table 1. Exclusion criteria

• Subjects in acute phase,

• Subjects aged under 30 and over 50

• Associated co-morbidities (i.e. metabolic syndrome)

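### The protocol contradicts itself on its primary contrast: the main aim is a before/after change, while H0 and the sample size compare OMT with sham

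*Protocol*

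**What the plan says.** Four places in the protocol bear on the primary contrast.

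- **Purpose of the Study, main aim.** The sentence opens "The main aim of the present randomized controlled two-arm and single-blind study is to evaluate the change in activation and connectivity", names the anterior insula, and ends with the "medial prefrontal cortex between before and after the period of manual treatment with osteopathic modality". Sham is not part of what is evaluated.
- **Purpose of the Study, secondary goal I.** The goal is "to monitor the differences of activity and FC of the SN between the study group and the sham control". The sham comparison is therefore ranked secondary, and it concerns a network rather than the two regions of the main aim.
- **MRI Data Processing.** Linear mixed effect models will evaluate "Differences in activity and connectivity pre / post or between groups in the insula and other regions of interest". No contrast is named as primary.
- **Statistic Analysis.** "The hypothesis H0 (null hypothesis) is the non-difference between the two groups at the end of the treatment". This is the only hypothesis stated. The effect size behind the sample size (d = 1.01) comes from a "comparison of connectivity values between different populations", "resulting in N=16 subjects per group". The Randomization section plans 20 per arm.

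**The concern.** The main aim and the hypothesis test answer different questions. A before/after change within the OMT arm combines any specific effect of the technique with whatever else changes over a month: natural course, repeated scanning, and the non-specific effect of being touched and attended to. The sham arm receives touch without technique so that these can be subtracted.

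Someone who takes the main aim at its word could report it as met on a significant pre/post change in the OMT arm, with the sham comparison reported separately as secondary. Someone who starts from H0 would judge the trial on the between-arm comparison. The protocol does not say which governs, so the choice could be made after the data are seen.

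**Working it through.** **Step 1. Which contrast was the sample size built for?**

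Inputs from Statistic Analysis: d = 1.01, and "an alpha and beta value of 0.05 and 0.8 respectively as usual in neuroimaging studies". I read the 0.8 as power and assume a two-sided test, since sidedness is not stated.

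Two independent groups, normal approximation:
n per group = 2 × (1.960 + 0.842)² / d² = 2 × 7.849 / 1.020 = 15.4, rounded up to **16**. This is the protocol's figure.

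Alternatives with the same inputs:

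| Calculation | n |
|---|---|
| Two groups, two-sided, normal | 15.4, i.e. 16 per group |
| Two groups, two-sided, t-test | 16.4 per group |
| Two groups, one-sided, normal | 13 per group |
| Paired pre/post, two-sided, t-test | 9.8, i.e. 10 in one arm |

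The stated 16 fits a two-sided comparison of two groups and does not fit a paired calculation. The trial was sized for the kind of comparison that the aims rank as secondary.

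**Step 2. What could happen if the main aim is followed as worded?**

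Suppose OMT has no specific effect and both arms drift by the same amount, δ, in units of the cross-sectional SD. Let r be the correlation between the first and last scan. Neither δ nor r is given in the protocol. I assume δ = 0.2, 0.3 or 0.5 and r = 0.5 or 0.7.

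- SD of the change = √(2(1 − r)): 1.000 for r = 0.5; √0.6 = 0.775 for r = 0.7.
- Standardised change = δ / SD of the change. For δ = 0.5 this is 0.500 and 0.645.
- The paired t-test with n = 20 has noncentrality √20 × standardised change: 2.24 and 2.89 for δ = 0.5.

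Probability of two-sided p < 0.05 in the OMT arm:

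| Shared drift (SD) | r = 0.5 | r = 0.7 |
|---|---|---|
| 0 | 0.050 | 0.050 |
| 0.2 | 0.136 | 0.195 |
| 0.3 | 0.247 | 0.376 |
| 0.5 | 0.565 | 0.782 |

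The between-arm test stays at 0.05 in every row, because a drift common to both arms cancels.

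Reading the two arms side by side does not solve this. With r = 0.5, the pattern of significant in OMT but not in sham has probability q(1 − q), where q is the table entry: 0.136 × 0.864 = 0.117 at 0.2 SD and 0.565 × 0.435 = 0.246 at 0.5 SD.

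**Step 3. Does the sample size survive the correction?**

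With 20 per arm and d = 1.01, a two-sample t-test has power 0.88 (0.79 with 16 per arm). If d is on the scale of end-of-treatment values, baseline adjustment multiplies the SD by √(1 − r²), which never exceeds 1. A change score multiplies it by √(2(1 − r)), which is at most 1 when r ≥ 0.5. So the stated N holds for the baseline-adjusted analysis, and for the change score provided r is at least 0.5.

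**The case against.** The strongest reply is that the between-arm test is already the confirmatory one. The main-aim sentence itself describes a randomised, controlled, two-arm study, the only H0 is between groups at the 0.05 level, and the sizing is two-group. No section specifies a paired test within the OMT arm or makes one a criterion of success.

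Much of this stands. A reader might infer that the trial is uncontrolled, or that its primary result has no type I error control. The documents do not support that: there is a randomised sham arm, and the stated hypothesis uses it. The between-arm H0 suggests that this contrast was intended. It does not remove the conflict, however. Where the authors want both kinds of comparison they say so, as goals II, III and IV do, and the main aim does not.

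A reader might also take goal I to be the main aim's between-arm version, merely demoted, and want to merge the two. Goal I concerns the salience network and gives no time point, so merging would widen the primary regions and add comparisons.

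The false-positive rates are also open to challenge. The protocol's introduction describes resting-state signal properties as stable between sessions, which argues against a large drift on those measures. Entry sets no threshold on pain severity or on any brain measure, so regression to the mean has no clear mechanism here. Both points are fair. They bear on how large the inflation is; any non-zero shared drift still pushes the within-arm rate above 5%.

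**Conclusion.** The concern holds as an internal contradiction about the primary contrast. The aim is worded as within-arm change, the H0 and sample size are between-arm, and the imaging section leaves both open. H0 also differs in quantity: it refers to a difference at the end of treatment, whereas the aim refers to change. No listed goal states a between-arm comparison of exactly the anterior insula and medial prefrontal cortex.

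If the aim's wording governed, the chance of a significant OMT-arm change without any specific effect would be roughly 14% to 78%. That range is illustrative. It rests on an assumed shared drift of 0.2 to 0.5 SD, a pre/post correlation of 0.5 to 0.7, 20 analysed OMT patients and a two-sided paired t-test. The contradiction itself rests on none of these assumptions.

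**What to change.** Make three wording changes together, since changing the aim alone would leave it at odds with H0.

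1. **Purpose of the Study.** State the main aim as the OMT-versus-sham difference in change from baseline to end of treatment in the anterior insula and medial prefrontal cortex, or as the difference in the baseline-adjusted end-of-treatment value. Keep goal I as a separate secondary goal for the salience network.
2. **Statistic Analysis.** Reword H0 to the same quantity and the same regions.
3. **MRI Data Processing.** Name this as the primary contrast of the mixed model. Report within-arm pre/post changes descriptively, with confidence intervals and no claim of efficacy.

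The baseline-adjusted form is the safer of the two, because it needs no condition on r to keep the stated sample size.

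The cost is an amendment to three sections. No patients, scans or procedures are added and the sample size stays as stated. The one loss is that a within-arm change alone can no longer be claimed as the primary result.

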**POPULATION STUDY**

*Study population*

The reference population of the study will consist of men and women aged between 30 and 50, suffering from chronic low back pain with a minimum period of pain of 6 months. Evaluation will follow the criteria published by Treede et al and the International Association for the Study of Pain (IASP) [33].

The exclusion criteria are shown in table 1.

Subjects who give their consent to participate in the study will be enrolled and randomly assigned to the study group or sham.

*Recruitment*

All the subjects belonging to the Physical and Rehabilitative Medicine Sector of the university of sports medicine (CUMS) of Chieti, will be recruited by an expert MD who will decide to include or exclude the participant from the study.

**STUDY / CONTROL GROUP**

*Randomization*

All patients included in the study are registered with a progressive identifier (patient code). The treatment arm will be assigned by random selection procedure. A computerized randomization algorithm based on the binomial distribution constructs a balanced and progressive list of random values ​​assigned within a specific interval (in this case 1 = group A, 0 = group B), this is also called randomization code. A progressive index is associated with each value. Treatment is assigned by assigning to each patient the randomization code relative to the equivalent patient code.

The randomization process will be based on the use of a software for randomization (R statistical software) [45] and conducted by a "permuted block" ratio of 1: 1.

The study foresees two groups (one of study and one of control) of 20 subjects each (= figure 1). The study group (OMT) will consist of 20 subjects who will receive osteopathic manipulative treatment. The sham control group will receive a similar touch without any technique.

**TYPE OF INTERVENTION**

*Study group*

Patients randomized in the study group will be treated with osteopathic modality; treatments will be performed with the following schedule: a weekly session for 4 treatments for a duration of 30 minutes. The treatments will be administered by 1 expert osteopath. The techniques used will be those of ligamentous-membranous-Guidance balancing, in line with the principles available in the literature. The treatments will be carried out at the Physical and Rehabilitative Medicine Sector of the University of Sports Medicine (CUMS) in Chieti.

*Sham control group*

Patients randomized in the sham group will receive treatment with the same timing and methodology applied to the study group. The treatments will be carried out by 1 healthcare professional with the same background. The sessions will be carried out at the Physical and Rehabilitative Medicine Sector of the University of Sports Medicine (CUMS) of Chieti.

All subjects will be asked during the treatment period (4 weeks) to avoid the use of drugs.

*Patient preparation*

Subjects will be instructed to simply keep their eyes closed, not to think about anything in particular and not fall asleep. After the session of the measurement session, the participants will be asked if they have fallen asleep during the recording, and the data of the subjects with positive and doubtful answer will be excluded from the study.

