**OUTCOMES**

*Functional Magnetic Resonance (fMRI)*

Acquisitions will be performed with a 3T MR tomograph at ITAB. The following recordings will be made with fMRI:

1) baseline

2) immediately after the first session

3) After 1 month, or at the end of the treatment period

The sequences that will be used are:

1) Eco-planar weighs in T2 * for fMRI measurements with contrast Blood Oxygenation

Level Dependent (BOLD) and Pseudo-continuous Arterial Spin Labeling (pCASL) for the Brain blood flow (CBF) measurements

2) Diffusion tensor imaging (DTI) sequences for the study of structural connectivity.

3) Spectroscopy sequences for the measurement of GABA concentrations.

The anatomical target will be the anterior insula.

*fMRI task*

A standard method to evaluate interoceptive and exteroceptive awareness will be used. This method is based on a paradigm already experimented in previous studies [27, 29, 46, 47]. This consists of three independent conditions presented in causal order for 15-20 sec each. The three conditions are: a task for IA, one for EA and a resting state period. The task of AI is to count own heart beats. EA's task is to count the rhythm of a sound stimulus, a piece of music, received in headphone. The period of fixation consists of voluntarily reducing cognitive activities to a minimum.

All the stimuli will be distinguished by a specific symbol on the display, which will also control the time for each individual task. When the task is finished, the subjects will report on a "visual analogue scale" the number of heart beats or rhythm deriving from the task.

*Diffusion Tensor Imaging (DTI)*

Structural connectivity will be investigated using the DTI, focusing on possible changes after the treatment period.

*Timing of instrumental acquisitions*

The instrumental acquisitions will last 50 minutes and will be divided as follows:

1) 5 'anatomical acquisition in T1

2) 10 'MRS

3) 10 'BOLD resting state

4) 5 'pCASL

5) 10 'DTI

6) 10 'BOLD TASK

*Questionnaires*

Patients included in the study will have to answer the following questionnaires in relation to the various times:

At inclusion

• General questionnaire with the purpose of collecting information on the social demographic status, drugs used, pain location and previous treatments.

• Temperament Evaluation of the Memphis, Pisa, Paris and San Diego - Autoquestionnaire (TEMPS-A). Self-administered questionnaire that measures temperament.

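### Read literally, the sleep rule removes randomised subjects from the study because of an event after treatment began, which conflicts with the unqualified intention-to-treat analysis

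*Protocol*

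**What the plan says.** Under TYPE OF INTERVENTION, Patient preparation, the Protocol says that after the measurement session "the participants will be asked if they have fallen asleep during the recording", and that "the data of the subjects with positive and doubtful answer will be excluded from the study". A doubtful answer counts the same as a yes. The rule names no sequence, visit or analysis set.

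Under POPULATION STUDY, "Subjects who give their consent to participate in the study will be enrolled and randomly assigned to the study group or sham". The order of the baseline scan and randomisation is not given.

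Under OUTCOMES there are three recordings: at baseline, "immediately after the first session", and "After 1 month, or at the end of the treatment period". Each lasts 50 minutes and comprises T1, MRS, resting-state BOLD, pCASL, DTI and task BOLD. The same section, in its list of questionnaires, says that "Patients included in the study will have to answer the following questionnaires in relation to the various times".

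Under STATISTIC ANALYSIS, "Statistical analysis will be based on the 'intention-to-treat' and 'per-protocol' method", and "The hypothesis H0 (null hypothesis) is the non-difference between the two groups at the end of the treatment". Neither analysis set is defined there, and the sleep rule is not assigned to either. MRI DATA PROCESSING plans linear mixed-effects models for the imaging comparisons.

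**The concern.** An intention-to-treat comparison keeps every randomised subject in the arm to which they were assigned. A rule that takes a subject's data out of the study because of something reported at a post-treatment scan does the opposite. This is not a detail left to a later plan. The Protocol fixes a rule and an analysis principle, and as written they cannot both be followed.

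Three things are at stake.

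- **Lost data.** The resting-state run is 10 of the 50 scanning minutes. Exclusion from the study would also discard the T1, DTI and MRS data (the last two serve secondary goals V and VI) and the pain, disability, mood, body-awareness and quality-of-life questionnaires. None of these is invalidated by dozing in a functional run.
- **Lost power.** Twenty per arm are planned against a calculated 16, so only four per arm are spare.
- **Possible selection.** One scan directly follows a hands-on session. If osteopathic treatment and sham leave people differently drowsy, the rule removes different people from the two arms, and the stated null hypothesis compares those arms.

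**Working it through.** **1. Do the two statements conflict?** The rule's unit is the subject's data and its scope is the study. Recordings 2 and 3 follow the first treatment and so must follow randomisation. No section limits the rule to a run, a visit or the per-protocol set. Followed literally, it takes randomised subjects out of a set that intention-to-treat requires to be complete.

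**2. The plan's own sample size.** Inputs from STATISTIC ANALYSIS: d = 1.01, alpha 0.05 (two-sided assumed) and 0.8. The Protocol labels the 0.8 as beta, but it is usable only as power.

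n per arm = 2(1.960 + 0.842)² / 1.01² = 15.4, rounded up to 16. The stated 16 reproduces. The two-sided t-test gives 16.4, that is 17. With the planned 20 per arm, t-test power is 87.5%.

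**3. Loss under the literal rule (illustration).** The documents give no sleep rate, so p, the chance of a yes or doubtful answer at one recording, is assumed. Sessions are assumed independent. If k recordings can trigger removal, 20(1 − p)^k per arm remain. Because the order of baseline scan and randomisation is unstated, k = 2 (baseline sleepers removed before randomisation and replaced) and k = 3 are both shown. The last column sets aside only the affected recording, which leaves 20(1 − p) at the end-of-treatment scan. Power is for a two-sided t-test at d = 1.01.

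| p | k = 2: n per arm, power | k = 3: n per arm, power | Affected recording only: n per arm, power |
|---|---|---|---|
| 5% | 18.1, 84% | 17.1, 82% | 19, 86% |
| 10% | 16.2, 79% | 14.6, 75% | 18, 84% |
| 15% | 14.5, 74% | 12.3, 67% | 17, 81% |
| 20% | 12.8, 69% | 10.2, 58% | 16, 79% |

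At 10%: 20 × 0.9² = 16.2, 20 × 0.9³ = 14.6 and 20 × 0.9 = 18.

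**4. Size of a possible bias (illustration).** Suppose there is no true effect, the outcome is standard normal, and the tendency to sleep is normal with correlation r to the outcome. Removing the sleepiest fraction q shifts the mean of those who remain by −r·φ(z)/(1 − q), where z is the (1 − q) normal quantile. The factor φ(z)/(1 − q) is 0.195 at q = 10% and 0.497 at q = 30%.

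- r = 0.2: 0.2 × (0.497 − 0.195) = 0.06 SD between arms.
- r = 0.5: 0.5 × (0.497 − 0.195) = 0.15 SD.
- Equal removal (20% and 20%) with the same r in both arms: 0.

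**The case against.** The strongest reply is that this is ordinary scan quality control. The sentence sits beside an instruction to lie with eyes closed, which fits the resting scan, and it speaks of sleep during the recording. Nothing says outright that questionnaires are dropped. The exclusion could also belong to the per-protocol set, or be treated as missing imaging data within intention-to-treat, and the planned mixed models can use incomplete series. This may well be what was meant, and setting aside a sleep-contaminated functional run is sound. But the text assigns the exclusion to the study, and nothing narrows it.

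Several limits on size stand in full. If baseline sleepers are screened out before randomisation, only two sessions count, and at 10% the arms stay at about 16. If the same people doze each time, losses shrink. With complete clustering at 10%, 18 per arm remain (84%).

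A reader might infer that the rule does bias the trial, or by as much as 0.30 SD. The documents do not support either inference. The larger figure needs sleep to be wholly determined by the outcome as well as a 10% v 30% split between arms, and nothing in the Protocol suggests either. Sham sessions have the same timing, and subjects and scanner operators are to be blinded. The drowsiness argument fits the second scan best, whereas the null hypothesis concerns the end of treatment.

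A reader might also take sleep to matter only for the resting run. Sleep in a counting task spoils that run too, so a repair limited to resting runs would be too narrow.

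**Conclusion.** The conflict in wording is real and holds whatever the sleep rate. A rule stated at the level of the study removes randomised subjects on an event at a post-treatment scan, while the analysis is declared intention-to-treat without qualification. It holds for recordings 2 and 3 even if the baseline scan precedes randomisation.

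The size is uncertain. At an assumed 10% per recording with independent sessions, the literal rule costs about 4 to 5 subjects per arm and brings power from 87.5% to between 75% and 79%. Setting aside only the affected recording costs 2 per arm at the final scan. At 5% the literal rule still leaves power above 80%.

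Bias is a possibility only. It requires sleepiness to differ by arm, or to relate differently to the outcome by arm. Under the assumptions shown it would be about 0.06 to 0.15 SD. The rule helps decide who is analysed for the main outcome, so it should be settled before data are seen.

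**What to change.** Replace the sentence under Patient preparation with:

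> Any wakefulness-dependent functional run (resting-state BOLD, pCASL or task) reported as slept or doubtful is set to missing for that run and visit only, decided without knowledge of arm. The participant and all other runs, visits and questionnaires stay in the intention-to-treat analysis (linear mixed model on all available visits). Whole-subject exclusion for sleep applies only to the per-protocol analysis.

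In addition:

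- ask about sleep run by run and record which run was affected;
- report slept and doubtful counts by arm and visit;
- add a sensitivity analysis that keeps the affected runs.

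The sensitivity analysis is needed because setting runs to missing recovers data and power but does not by itself remove selection bias in the affected outcomes. If missingness depends on the unobserved signal, the mixed model is not protected.

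The cost is one paragraph of text, a slightly longer post-scan question and one extra analysis. Some runs will be missing, and the sensitivity analysis will contain drowsy scans.
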